## Abstract

**Background:**

Automatic processes to approach smoking-related cues have been repeatedly linked to smoking status, intensity of smoking, and cigarette craving. Moreover, recent findings suggest that targeting those tendencies directly by means of approach bias modification (ABM) has merit in changing maladaptive approach tendencies for drug cues and reducing drug consumption. However, training effects tend to be small. Embedding the training into virtual reality (VR) technology could be a promising way to improve training efficacy. The present protocol describes a randomized controlled trial that aims to assess the efficacy of a newly developed VR-ABM as a means of reducing smoking-related approach biases or nicotine consumption in smokers seeking abstinence.

**Methods:**

One hundred daily smokers who are motivated to quit smoking will be recruited into the randomized controlled trial. All participants will attend a brief smoking cessation intervention (TAU) and will be randomly assigned either to the experimental (VR-avoidance training) or the placebo-control group (VR-placebo training). During the VR-avoidance training, participants are implicitly instructed to make an avoidance movement in response to smoking-related objects (e.g., cigarettes) and an approach movement in response to alternative objects (e.g., healthy food). During the VR-placebo training, no such contingency between arm movement and item content exists. Trainings are administered in six sessions within two weeks. Training effects on automatic approach tendencies and smoking behavior are measured immediately after training and at a 7-week follow-up.

**Discussion:**

Embedding the training into virtual reality (VR) technology could be a promising new way to improve ecological validity, realism, and immersion and thereby increase ABM training effects. The results of this study can inform future research in the optimization and advancement of treatment for addiction.

**Trial registration:**

Registered with Current Controlled Trials: study ID ISRCTN16006023. Registered on 28 March 2019.

## Background

Tobacco smoking remains the most preventable cause of premature death and morbidity worldwide. While most smokers are aware of the detrimental effects related to smoking, and most smokers desire to quit smoking, common behavioral interventions for smoking are of limited efficacy. Even following effective treatment, fewer than 25% of smokers manage to remain abstinent for at least 6 months [1–3]. Thus, an urgent need exists for the development of more effective treatment options and the improvement of efficacy of existing smoking cessation interventions.

One potential reason for these discouraging outcomes might be that addictive behavior is not only driven by explicit, rational, or reflective processes that are usually targeted, by traditional treatments but also by implicit, hard to control, automatic processes [4, 5]. In line with this notion, dual process models of addiction [6, 7] propose that both limited reflective processes *and* strengthened impulsive processes are the key determinants of addiction development, maintenance, and treatment. The latter processes are supposed to be implicated in the formation of so-called information-processing or *cognitive* biases. That is, as addiction progresses, information processing is biased in favor of drug-related cues, making drug taking more likely. The approach bias for smoking can be defined as the automatic tendency to approach smoking-related cues and is of special interest because of its strong connection with cigarette craving and actual smoking behavior [8, 9].

Most recently, the Approach-Avoidance Task (AAT)—originally designed to assess automatic avoidance tendencies in spider-anxious individuals [10]—has proven useful in both measuring and modifying approach biases for appetitive behaviors, including smoking [8, 9]. During the task, various images appear on a computer screen. Participants are instructed to ignore image content and to respond to a content-irrelevant feature such as image format or orientation by either pulling or pushing a joystick attached to the computer. Upon a pull movement, the picture increases in size, whereas upon a push movement, the picture shrinks. This zooming feature disambiguates the task and creates a visual sense of approach and avoidance. An approach bias is inferred from faster pulling than pushing of a picture of interest. Hence, the AAT can be viewed as a measure of performance deficits due to the incongruence between the instructed movement and the automatically triggered response. Using the AAT, an approach bias for cigarette cues was found in smokers but not in ex-smokers or those who have never smoked [9]. A study conducted by Watson and colleagues [11] showed that acute exposure to nicotine (i.e., smoking a cigarette) led to an increased nicotine-related approach bias. Finally, a study by our own working group [8] showed that smokers display an automatic approach bias for smoking cues but not for natural rewards (such as highly palatable food).

Throughout the last decade, a large body of research has shown that experimental tasks originally developed to measure cognitive biases also have merit in modifying such biases, sometimes leading to improved health behavior [4]. For instance, the AAT has been adapted to a training variant by changing the contingency between picture content and arm movements. In the training version of the task, smoking-related pictures are consequently presented in the push-away format, while alternative pictures are presented in the pull-closer format. Recently, we applied four sessions of AAT-training as an add-on to a brief smoking cessation intervention to a sample of inpatient psychiatric smokers [12]. Compared to sham training, the AAT-training led to a larger reduction of nicotine consumption at a 3-month follow-up. In a related study, smokers seeking abstinence were assigned to four sessions of AAT-training or sham training and were instructed to make a self-guided quit attempt upon completion of the final training session [13]. The reduction in approach bias emerged as being positively related to the number of days abstinent following the quit attempt. Hence, upcoming evidence suggests that approach bias retraining by means of the AAT might be a useful intervention to reduce smoking or promote abstinence. Similarly, several reviews and meta-analyses support the above-mentioned results and give rise to the premise that approach bias retraining has merit in changing addictive behaviors [4, 5]. However, the effects tend to be small or sometimes even mixed [14]. Thus, improving training efficacy constitutes a key challenge for cognitive bias modification (CBM) programs.

Although the exact training mechanisms remain uncertain, cognitive bias trainings apparently must be administered multiple times to generalize to real-world behavior and to produce reliable and stable changes over time. This requires participants to be willing to maintain adherence to a daily or weekly training prescription. However, adherence to the trainings might be limited, as trainings are often perceived as monotonous or boring. Confirming the above-mentioned concerns, preliminary evidence suggests that high dropout rates can be challenging for CBM studies [12, 15, 16]. Another reason for rather small training effects concerns the generalization of training to actual everyday behavior. It has been argued that the interaction with simple two-dimensional images reduces the realism of the training and thereby narrows the ecological validity of the task [17]. Virtual reality (VR) simulates a natural environment by presenting an interactive three-dimensional space that mirrors everyday-like arm or posture movements [18]. The realism and immersion created by VR can reasonably be assumed as possibly contributing to the ecological validity and enhancing the engagement, enjoyment, and—most importantly—training adherence [19]. Therefore, this study introduces a novel VR approach bias training (VR-AAT) for smoking as an add-on to brief behavioral counseling for smoking cessation. Our objective is to investigate whether the newly developed VR-AAT is capable of modifying existing approach biases for smoking cues and/or changing smoking behavior by promoting abstinence or reduction of nicotine consumption. The study utilizes a randomized placebo-control design and multi-session VR training during a 2-week training period. We expect that the VR-AAT would reduce smoking-related approach biases as measured with the assessment version of the AAT [8], reduce the number of daily smoked cigarettes, and increase abstinence rates over and above the placebo-control condition.

## Methods/Design

### Trial design

The present study is a randomized control trial comparing self-report, behavioral, and biochemical outcomes of the VR-AAT training to an active placebo control condition (Additional file 1). Smokers are randomly assigned either to the experimental (brief smoking cessation intervention, hereafter referred to TAU + VR-avoidance training) or to the sham-control condition (TAU + VR-placebo training). This study employs a 2 (condition: avoidance training vs. placebo training) × 3 (time: pretest/post-test: 3 weeks after baseline/follow-up: 7 weeks after baseline) mixed design. Because we expect the experimental condition to be more effective than the sham-training control condition, this protocol describes a superiority trial design. The training intervention occurs over the course of 2 weeks in which smokers complete six training sessions in total. Measures of cognitive biases (approach, attention, and association bias), self-report measures of smoking behavior and biochemically verified smoking intensity are applied at the pretest, post-intervention, and 7-week follow-up.

A priori power analyses were conducted using G*Power 3.1 (open-source software) [20]. Previous research on the efficacy of CBM trainings found a small to moderate effect size [12, 21]. We conducted a power analysis for a 2 × 3 mixed design ANOVA to detect a small-to-moderate effect (Cohen’s d = .30). Our results indicated that a total sample size of 74 is required to achieve 80% power at an alpha level of 0.05 and an assumed correlation of r = .50 between the repeated measures. Because we expect some attrition due to our multisession design, we decided to include 100 participants, which is 50 per condition.

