### Data preparation and planned analyses

So that missing data can be filled in, multiple imputation and the modified Intention-To-Treat (ITT) principles [36] will be used. Prior to computation of the cognitive bias scores, error trials will be excluded from further analyses. Median reaction times will be used to minimize the influence of outliers.

To test for changes in cognitive biases, mixed design ANOVAs will be calculated. Due to random assignment to the experimental or to the placebo group, we expect a priori group differences to be small. Possible chance baseline imbalance between treatment arms will be taken into account by means of follow-up simple effects analyses. For approach biases, a 2 (condition: VR-avoidance training vs. VR-placebo training) × 2 (item content: smoking vs. control items) × 3 (time: pretest, post-test, follow-up) mixed design ANOVA will be conducted. For attentional and association biases, two separate 2 (condition) × 3 (time) mixed design ANOVAs will be calculated.

To evaluate the effects of training on self-reported average daily nicotine consumption, a 2 × 3 mixed ANOVA will be carried out in which the training condition is a between-subjects factor and time (pretest, post-test, follow-up) is a within-subjects factor.

Multilevel modeling (MLM) will be used to estimate the growth curve for nicotine consumption as measured with the cigarette-training app and craving ratings over time.

To explore whether the VR-training leads to increased abstinence rates, a Chi-square test will be computed.

To test the effect of training on other smoking-related variables (i.e., CO, FTND, smoking attitude, motivation to quit), a 2 (condition) × 3 (time) repeated measures MANOVA will be conducted. Significant multivariate effects will be followed up with separate ANOVAS on each dependent variable. In case of significant interactions, discriminant factor analyses will be conducted to identify possible associations between each of the dependent variables and group assignment.

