### Trial status

This trial was registered on 28 March 2019 (registration number ISRCTN16006023, protocol version number 1.0). As of November 2019, 108 participants have been enrolled in the study. The first participant was enrolled in 23 March 2019, and completion of recruitment is projected for December 2019. The final results will be published as soon as possible after the analysis is completed.

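### The 80% power quoted for 74 participants belongs to interaction f = .15, not to Cohen's d = .30; with d = .30 at both later visits, power is about 24% at 74 and 32% at 100

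*Protocol article*

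**What the plan says.** The sample-size paragraph in Trial design gives every input but one. The design: "We conducted a power analysis for a 2 × 3 mixed design ANOVA". The effect: "to detect a small-to-moderate effect (Cohen’s d = .30". The result: "Our results indicated that a total sample size of 74 is required to achieve 80% power at an alpha level of 0.05", with "an assumed correlation of r = .50 between the repeated measures". The total was then raised to 100 (50 per arm) for attrition. The missing input is the effect size f that G*Power takes for this test. The paragraph also does not say which term of the ANOVA was powered, or at which visits the arms are supposed to differ by d.

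Under Data preparation and planned analyses, self-reported daily consumption is tested by a 2 × 3 mixed ANOVA. Approach bias is tested with a further factor ("item content: smoking vs. control items) × 3 (time: pretest, post-test, follow-up) mixed design ANOVA will be conducted"), and abstinence by a chi-square test. The same section expects arm differences at baseline to be small because of randomization.

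**The concern.** In a randomized trial with a pretest, the training effect in a 2 × 3 mixed ANOVA is the condition × time interaction. An interaction f is not half of a between-arm d: part of any post-training difference is absorbed by the condition main effect, and only the departure from the average difference counts. If d was simply halved, the paragraph promises 80% power for an effect that the test would detect far less often.

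The Background section says that effects of this type of training tend to be small. A reader who trusts the 80% could take a non-significant interaction as evidence against an effect of 0.30 SD, when the design could not support that conclusion.

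**Working it through.** **Inputs.** From Trial design: 2 arms (k = 2), 3 visits (m = 3), correlation ρ = .50, α = .05, N = 74 or 100. From Randomization and blinding: 1:1 allocation. From Trial status: N = 108, used only as a further sample size. Assumed by me: sphericity, no attrition, d in units of the SD at a single visit.

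**Formula.** For the within-between interaction, the noncentrality is λ = N·m·f²/(1 − ρ), with df1 = (k − 1)(m − 1) = 2 and df2 = (N − k)(m − 1) = 2(N − 2). Power is the upper tail of the noncentral F beyond the 5% critical value.

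**Step 1: reproduce 74.** Take f = .30/2 = .15.
- N = 72: λ = 72 × 3 × .0225/.5 = 9.72; power 79.5%.
- N = 74: λ = 74 × 3 × .0225/.5 = 9.99; power 80.6%.

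So 74 is exactly the answer for f = .15. The alternatives tried do not give it:
- interaction with f = .30: 20
- between-arm main effect with f = .15: 236
- G*Power's two other effect-size conventions with f = .15: 218 and 430
- two visits instead of three, f = .15: 90
- two-sample comparison of means at d = .30: 350 (two-sided) or 276 (one-sided)

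**Step 2: the f that d = .30 implies.** Let the arm differences at the three visits be (0, d, d). Their mean is 2d/3, and the departures from it are (−2/3, 1/3, 1/3)d. Each arm carries half, so the interaction effects are ±(1/3, 1/6, 1/6)d. The mean square is (1/9 + 1/36 + 1/36)d²/3 = (1/6)d²/3 = d²/18. Hence f = d/√18, and d = .30 gives f = .0707.

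**Step 3: power at that f (f² = .005).**

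| N | λ | Power |
|---|---|---|
| 74 | 74 × 3 × .005/.5 = 2.22 | 24.2% |
| 100 | 3.00 | 31.7% |
| 108 | 3.24 | 34.0% |

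Simulation of the interaction test (20,000 trials each) gave 24.5% at 74 and 31.6% at 100. For scale, 80% power under this pattern would need about 324 participants.

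**Step 4: other patterns of arm difference, N = 74.**

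| Pattern (pretest, post-test, follow-up) | f | Power |
|---|---|---|
| 0, .15, .30 | .061 | 19% |
| 0, .30, 0 | .071 | 24% |
| 0, .30, −.30 | .122 | 62% |
| −.30, .30, .30 | .141 | 76% |

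The last row is the largest f possible when no difference exceeds 0.30 SD. It is also unrealistic under randomization, since it needs a pretest difference in the opposite direction.

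**Step 5: what the design can detect.** Exactly f = .15 corresponds to d = .15 × √18 = 0.64. The effect that gives exactly 80% is f = .149, or d = 0.63, at N = 74; and f = .128, or d = 0.54, at N = 100.

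**The case against.** The strongest defence is that nothing was miscalculated: 74 is correct for f = .15, and the paragraph never defines what d contrasts. If d is shorthand for twice the interaction f, the sentence is opaque but not false. It is true that the calculation itself was carried out correctly for its input. But the paragraph names Cohen's d, which a reader takes as a standardized difference between arms, and nothing there signals another meaning. Reading d on the change-score scale does not help either: at ρ = .50 the SD of a change is √(2 × .5) = 1 times the SD at one visit.

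The percentages also depend on an assumed pattern. That stands, and the pattern must be stated with them; but no pattern within 0.30 SD reaches 80% at 74.

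A reader might infer more than the documents support:
- **That the approach-bias test falls wholly outside the calculation because it is a three-way interaction.** The three-way interaction is algebraically the 2 × 3 interaction on the smoking-minus-control difference, so the calculation applies if the effect is expressed on that scale. A separate power figure would need assumptions about the control-item bias that the article does not supply.
- **That abstinence has a specific low power.** The paragraph claims no power for it, and gives no abstinence rates from which to compute one.
- **That 108 enrolled against a planned 100 shows a planning error.** "As of November 2019, 108 participants have been enrolled in the study" is a dated status note and does not show that the planning figure was wrong when set.
- **That all planned tests are weak at d = .30.** The multilevel growth models for app-logged consumption and craving were not examined here.

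**Conclusion.** The point holds. The stated design, d, correlation, α, power and N cannot all be true together. The fault is the effect-size label: f = d/2, a two-group main-effect conversion, was evidently applied to a condition × time interaction. With equal arms at pretest, the same d at post-test and follow-up, sphericity, ρ = .50 and no attrition, power at d = .30 is about 24% at 74, 32% at 100 and 34% at 108, against a stated 80%. Attrition would lower these figures. The percentages belong to that pattern; the failure to reach 80% at N = 74 does not depend on it, provided no arm difference exceeds 0.30 SD. This is a wrong statement that is printed in the article, so neither the condensed format nor an analysis plan that is not shown explains it. It does not invalidate the planned analyses or their type I error.

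**What to change.** Rewrite the sample-size paragraph, without enrolling more participants, to say that:
- N = 74 gives 80% power for a condition × time interaction of f = .15, which is a between-arm difference of about 0.64 SD at both post-test and follow-up with none at pretest;
- the difference detectable with 80% power under that pattern is about 0.63 SD at 74 and 0.54 SD at 100;
- power at d = .30 under the same pattern is about 24% (74) to 32% (100), assuming sphericity and no attrition;
- the calculation makes no power claim for the chi-square test of abstinence, and applies to the three-way approach-bias test only if the effect is expressed on the smoking-minus-control difference scale.

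Delete the claim of 80% power at d = .30. The cost is wording only: no analysis or recruitment changes, but the stated power becomes less favourable. The correction should be in place before the results are interpreted.

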### Participants

Current smokers (*n* = 100) will be recruited at the University of Siegen (Germany) and from the general population. Figure 1 provides a CONSORT diagram of the participant recruitment. Participants will be recruited through flyer advertisements, radio broadcasts, television reports, newspaper reports, and web advertisement. Interested participants will receive information regarding the study via e-mail and will be invited to take part in a telephone interview to assess eligibility criteria. Smokers will be included if they smoked more than six cigarettes per day during the last 6 months. Exclusion criteria are current alcohol or drug misuse or dependency, psychiatric illness, insufficient German language skills, or uncorrected visual or auditory impairment. Participants enrolled in the study complete nine sessions in total, which are composed of three laboratory assessment sessions (pretest, post-test, and 7-week follow-up) and six VR-training sessions (carried out between the pretest and post-test). Full written informed consent will be obtained from each participant at study entry.

**Fig. 1 Fig1:**
[figure not shown]
CONSORT flow diagram

### Ethics statement

The study protocol (version 1: 05/2019) was approved by the local Ethics Committee of the University of Siegen (reference number: ER_18_2018) and was conducted in accordance with the Declaration of Helsinki and Good Clinical Practice guidelines. During the course of the study, ethical, legal, and social aspects (ELSA) will be anticipated and addressed. Each participant will provide a written informed consent to the experimental procedure prior to the inclusion in our study. Participation will be entirely voluntary and participants will have the right to withdraw their consent for participation at any time.

### Randomization and blinding

Participants will be randomly assigned to the experimental or placebo control group, according to an externally constructed randomization plan. The ratio will be 1:1. A computer-generated randomization schedule will be employed by means of a computerized random number generator using IBM SPSS Statistics 24. Permuted block randomization will be used to ensure that study groups of approximately the same size are generated. Block size will be set to 50 participants. No other stratification will be used. Although participants will be blind to the experimental conditions, blinding of the assessors is not possible because of the course of the study (single-blind trial). In addition, a training evaluation questionnaire will be employed at post-test and follow-up, which will serve as a manipulation check in order to examine whether single-blinding was possible. To avoid bias in the outcome assessment, research assistants concerned with data collection and/or preparation will be blind to the allocation of the participants.

### Intervention

Prior to the training, participants take part in a brief psychoeducational workshop containing information on nicotine addiction, the short- and long-term effects associated with cigarette smoking, and behavioral approaches to smoking cessation (approximately 60 min). Afterward, smokers receive a self-help book (“The Easy Way to Stop Smoking” by Allen Carr) to aid smoking cessation and will be instructed to record their daily intake of cigarettes by using a mobile phone application specifically developed for this study (Cigarette Tracking List, SenseAble UG). According to the dual-process models of addiction, these behavioral approaches should target reflective processes associated with smoking, resemble traditional smoking cessation interventions, and therefore constitute our TAU intervention. To address more automatic, impulsive processes, participants receive either the VR-avoidance training or the VR-placebo training according to the predefined randomization plan.

